### Outcomes

The primary outcomes include serum levels of biochemistry parameters except ALT and AST. The secondary outcomes are ALT and AST, body composition, PA, BP, HRQOL, and dietary intake. The primary and secondary outcomes will be conducted at the baseline and the end of the study (day 90 after intervention) for all participants. Only adherence will be checked at the end of every month.

### Outcome measurements

All outcomes and time points are specified in Fig. 2.

### Demographic and medical information

The demographic and medical history data include gender, age, full address, postal code, marital status, income, occupation, ethnicity, educational background, smoking history, alcohol consumption, family history of diabetes or/and hypertension, medication history (dosage and type of drugs), and the diagnosis time of prediabetes.

### Anthropometric data

Weight and height will be measured using a pre-calibrated electronic scale (Seca, Germany) to the nearest 0.5 kg and a wall-mounted stadiometer to the nearest 0.1 cm, respectively. BMI (kg/m^2^) will be calculated by the following equation: weight (kg)/height (m^2^). A non-elastic and flexible tape will be used to measure WC (at the midpoint between the iliac crest and the rib cage in a standing position at the end of normal expiration) and HC (the level of the greater trochanters) to the nearest 0.1 cm.

WHtR and WHR will be calculated by dividing WC by height and WC by HC, respectively. The ABSI was calculated using the following formula: ABSI = WC (m)/(BMI^2/3^ × height^1/2^ (m)) [48].

Body composition will be estimated using the bioelectrical impedance analysis (BIA) method by a body composition analyzer (InBody 270, Seoul, South Korea).

All anthropometric assessments will be conducted by a trained assessor in duplicate, with the mean measurement recorded.

### Blood pressure

According to the American Heart Association protocol, BP will be measured at the baseline and at the end of the study by an assessor under the following conditions:

After 5 min of rest in a quiet place, the participants will be sitting without crossed legs and unsupported back and arms. The BP of the participants will be measured in both arms by the Korotkoff sound technique with a calibrated mercury sphygmomanometer (Omron, Tokyo, Japan). If a consistent difference in BP measurement between the arms is shown, the maximum pressure will be recorded. The mean of three readings will be recorded (1-min interval between them) [49].

### Laboratory investigations

Blood samples (12 ml) of all participants will be collected after 12 h of overnight fasting at the baseline and at the end of the study. The samples will be collected into two different tubes (in the tube without anticoagulant and in EDTA tubes) and centrifuged to obtain the serum or plasma. The serum samples (3 ml) will be stored at − 80 °C. The plasma and the remaining serum will be used to determine the FPG, 2hpp (glucose oxidase/peroxidase method, BioSystem, Spain), HbA1c (HPLC, TOSOH, Japan), TG (glycerol phosphate oxidase/peroxidase method, BioSystem, Spain), TC (cholesterol oxidase/peroxidase method, BioSystem, Spain), HDL-C (direct method, BioSystem, Spain), SOD (colorimetric (420 nm) method, ZellBio GmbH, Germany), TAC (colorimetric (570 nm) method, ZellBio GmbH, Germany), MDA (colorimetric (535 nm) method, ZellBio GmbH, Germany), ALT, AST (IFCC method, BioSystem, Spain), serum insulin (enzyme-linked immunosorbent assay (ELISA) kit, Monobind, USA), serum zinc (flame atomic absorption spectrometry method (Ziest Chem Diagnostics kit, Iran), serum IL-1B (human IL-1β (ELISA kit), BE58011, IBL, Hamburg, Germany), and serum hs-CRP )ELISA kit, EU59131, IBL, Hamburg, Germany). At least 1 ml of random urine specimen (the fasting state is not necessary for urine collection) will be taken at the baseline and at the end of the study for the measurement (urine zinc by flame atomic absorption spectrometry method (Ziest Chem Diagnostics kit, Iran; normal range 15–150 μg/dl). All biochemical tests except IL-1B, hs-CRP, SOD, TAC, and MDA will be conducted immediately after sampling.

The following formula will be used to calculate VLDL and LDL-C:
VLDL = TG (mg/dl)/5 (this formula is valid only when TG are ≤ 400 mg/day)LDL-C = TC (mg/dl) − HDL-c (mg/dl) − TG (mg/dl)/5; Friedewald formula [50].

The homeostasis model of assessment 2 (HOMA-2) calculator will be downloaded from the University of Oxford and used to calculate IR, S%, and BCF% (http://www.dtu.ox.ac.uk/).

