#### Primary objective

The primary objective is to compare the mean changes in the serum levels of biochemical parameters (fasting plasma glucose (FPG), 2 h post-prandial (2hpp), HbA1c, serum insulin, insulin resistance (IR), insulin sensitivity (IS) %, beta cell function (BCF) %, TG, TC, LDL-C, high-density lipoprotein (HDL), very low-density lipoprotein (VLDL), total blood antioxidant capacity (TAC), malondialdehyde (MDA), serum zinc, urine zinc, serum interleukin-B (IL-1B), and high-sensitivity C-reactive protein (hs-CRP)) between the groups.

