## Method

### Study design

The flow chart of the study design and the schedule of enrollment, interventions, and assessments are shown in Figs. 1 and 2, respectively. The participant will be randomized in a 2 × 2 factorial design into four parallel treatment groups: (1) curcumin group (Cur/P.Zn), curcumin supplement + placebo for zinc; (2) zinc group (Zn/P.Cur), zinc supplement + placebo for curcumin; (3) zinc + curcumin group (Zn/Cur), zinc supplement + curcumin supplement; and (4) placebo group (P.Zn/P.Cur), placebo for curcumin and zinc. The follow-up duration will be 3 months (90 days).

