### Sample size

The sample size was determined based on the ability to detect a mean effect of FPG between the supplement and placebo groups for each supplement (curcumin or zinc), separately.

By using the following formula, the maximum sample size for curcumin group based on the trial by Chuengsamarn et al. [26] and zinc group based on the trial by Ranasinghe et al. [40] was determined to be 8 ($$ {\overline{X}}_1 $$ = 3.64, $$ {\overline{X}}_2 $$ = − 7.54, *S*_1_ = 8.17, and *S*_2_ = 7) and 19 ($$ {\overline{X}}_1 $$ = + 16, $$ {\overline{X}}_2 $$ = + 3, *S*_1_ = 12.8, and *S*_2_ = 15.3), respectively (*α* = 0.05, significance; *β* = 0.2, power). Then, the maximum sample size was considered as the final sample size, which is sufficient to evaluate the main effects. According to an expected 10% loss at follow-up, 84 subjects (21 participants in each group) will be recruited, finally.

$$ {n}_1=\frac{\left({S}_1^2+{S}_2^2\right){\left({Z}_{1-\frac{\alpha }{2}}+{Z}_{1-\beta}\right)}^2}{{\left({\overline{X}}_1-{\overline{X}}_2\right)}^2} $$

In the formula above, *S*^2^ and $$ \overline{X} $$ show the variance and the mean effect for FBS in the placebo and treatment groups, respectively. Also, for a more accurate calculation of the sample size, the WinPepi statistical program (version 11.4: Abramson, 2011) was performed.

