### Intervention

The dose of supplements was calculated based on the data from the previous studies [26–32, 39, 40, 44]. A dose of 30 mg/day of zinc as zinc gluconate for 3 months will be prescribed. A dose of 30 mg/day zinc element as zinc sulfate significantly improve FPG, BCF, IS, and IR for 6 months, whereas 20 mg/day of zinc element had a favorable effect on FPG, OGTT, IR, TC, LDL-C, and BCF but for 12 months. Also, the cytotoxicity of zinc gluconate was less than that of zinc sulfate. The effect of curcumin extract on the patients with IFG, IGT, and MeS has been seen with different doses ranging from 20 to 2400 mg and follow-up duration between 2 and 9 months.

Zinc supplement contains 30 mg zinc as zinc gluconate. The curcumin supplement (BCM95/Curcugreen) used in the study is an extract of dried turmeric rhizomes which was identified by a qualified botanist as *Curcuma longa*, and a voucher specimen is kept with herbarium ID HERB-ED-22. The turmeric rhizomes were extracted with ethyl acetate, and each 500-mg capsule of curcumin supplement contained 475 mg of curcuminoids and turmeric essential oil. The purity of the bioactives in the capsule was tested by HPLC, residual solvents by GCHS, and heavy metals by ICPMS, and microbial parameters conformed to the EU standards. Placebos are identical in texture and appearance to its active supplement. The placebo for zinc is made of lactose (that was produced in the School of Pharmacy, Shahid Sadoughi University of Medical Sciences and Health Services, Iran), and the placebo capsules for curcumin are made of roasted rice powder (that was produced by “M/s Arjuna Natural Pvt Ltd., India.” All participants will receive a tablet (zinc supplement or placebo for zinc) to be consumed before breakfast and a capsule (curcumin supplement or placebo for curcumin) to be taken after breakfast, daily. Also, the energy requirement of the participants will be calculated by the report of a Joint FAO/WHO/UNU Expert Consultation [45], individually. Given that the participants are overweight or obese, they will receive a standard hypo-caloric diet with at least a 7% weight loss [46] including 45–55%, 25–35%, and 10–20% of their calories from carbohydrate, fat, and protein, respectively [47].

In each visit (visit 1, 1st day; visit 2, 30th day; visit 3, 60th day), the health information (diet and physical activity) will be recommended to all participants to improve healthy habits, individually.

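### Urine zinc is a raw concentration in one untimed spot specimen per visit with no dilution marker, so its 90-day change carries avoidable noise from urine dilution

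*Protocol article*

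**What the plan says.** The Laboratory investigations section of the protocol article fixes each element of the urine zinc measurement.

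- **Specimen:** "At least 1 ml of random urine specimen (the fasting state is not necessary for urine collection) will be taken".
- **Occasions:** it "will be taken at the baseline and at the end of the study for the measurement". That is one specimen at each of two visits; the Study design section sets follow-up at 90 days.
- **Assay and unit:** flame atomic absorption, with a "normal range 15–150 μg/dl".

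The assay list in that section is detailed, down to kit numbers for some analytes. It has no urine creatinine, specific gravity, osmolality, urine volume or timed collection.

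The status of urine zinc varies from place to place. The Primary objective section compares mean changes in a list that includes "serum zinc, urine zinc, serum interleukin-B (IL-1B), and high-sensitivity C-reactive protein (hs-CRP)) between the groups". The Outcomes section says "The primary outcomes include serum levels of biochemistry parameters except ALT and AST", which does not cover a urine measure, and its secondary list omits urine zinc too. The Abstract's Methods paragraph puts urine zinc among the additional assessments, alongside liver enzymes and blood pressure.

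The Statistical analysis section compares changes between four groups by one-way ANOVA with LSD (or Kruskal-Wallis). It reports a percentage change from baseline for every variable and uses ANCOVA only if judged necessary.

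**The concern.** For a fixed rate of zinc excretion, the concentration in a spot specimen falls as urine volume rises. A participant who drank more before one visit than before the other shows a change in μg/dl with no change in zinc excretion. Nothing described as measured in the specimen can separate the two, and no dilution variable exists that an ANCOVA could use.

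This is separate from when the last zinc tablet was taken. Fixing the sampling time relative to the tablet would leave dilution variation in place.

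At stake is the precision of one outcome listed under the primary objective. The planned percentage change makes matters worse, because the noisy baseline value becomes the denominator.

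**Working it through.** **The plan's own figures.** The article gives no sample size, SD or effect for urine zinc: "The sample size was determined based on the ability to detect a mean effect of FPG between the supplement and placebo groups". That FPG calculation reproduces, with (1.960 + 0.842)² = 7.849:

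- Curcumin: (8.17² + 7²) × 7.849 / (3.64 + 7.54)² = 7.27, so 8.
- Zinc: (12.8² + 15.3²) × 7.849 / (16 − 3)² = 18.48, so 19.
- Adding 10% gives 20.9, so 21 per group and 84 in all.

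It says nothing about urine zinc, but it sets the pairwise comparison at about 19 v 19 after losses (21 × 0.9 = 18.9).

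**Anchor from the article.** If 15–150 μg/dl is read as a central 95% range on a log-normal scale (an assumption), the log SD of a single result is ln(150/15) / (2 × 1.96) = 0.587. This total also contains differences between people, so it caps the within-person SD and does not isolate dilution.

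**Model.** On the log scale, with dilution independent of everything else:

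- Within-person SD = √(d² + o²), where d is the dilution SD and o is the SD of all other within-person variation.
- SD of change = √2 × √(d² + o²).
- Dilution share of the variance of change = d² / (d² + o²).

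Assumptions: o = 0.30, d = 0.2 to 0.5. At d = 0.5 the within-person SD is √(0.25 + 0.09) = 0.583, which already uses up nearly all of the 0.587. At d = 0.6 it would be 0.671, above the cap, so that case is left out.

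**Power.** Assumed true effect: a 40% rise, ln 1.4 = 0.3365. Two-sided 0.05, 19 v 19, noncentral t with 36 df and noncentrality 0.3365 / (SD of change × √(2/19)). The smallest detectable ratio at 80% power is exp(2.80 × SD of change × √(2/19)).

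| d | SD of change | Dilution share | Noncentrality | Power, 40% rise | Power, doubling | Smallest detectable ratio |
|---|---|---|---|---|---|---|
| 0 (fully corrected) | 0.424 | 0% | 2.44 | 66% | >99% | 1.47 |
| 0.2 | 0.510 | 31% | 2.03 | 51% | 98% | 1.59 |
| 0.3 | 0.600 | 50% | 1.73 | 39% | 93% | 1.73 |
| 0.4 | 0.707 | 64% | 1.47 | 30% | 84% | 1.90 |
| 0.5 | 0.825 | 74% | 1.26 | 23% | 71% | 2.12 |

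The doubling column uses ln 2 in place of ln 1.4. If the factorial margin were analysed instead (38 v 38), power for a 40% rise would be 81%, 67%, 53% and 42% for d = 0.2 to 0.5, against 93%.

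**Wider range.** Letting both SDs run from 0.2 to 0.5, the dilution share runs from 0.04/0.29 = 14% to 0.25/0.29 = 86%. The upper corners of this grid exceed the 0.587 cap.

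**Bias.** In a simulation with no treatment effect and dilution independent of arm (d = 0.5, o = 0.3, 38 v 38), the mean group difference was about 0 and the type I error 0.049.

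**Percentage change.** With no true change, the mean of E/B under this model is exp(d² + o²). The expected percentage change is then exp(0.09) − 1 = 9% without dilution noise, exp(0.18) − 1 = 20% at d = 0.3 and exp(0.34) − 1 = 40% at d = 0.5. With no treatment effect this falls on all arms alike, but a placebo arm read by itself would seem to show rising zinc excretion.

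**The case against.** The strongest case on the other side has six parts.

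- **The size is assumed.** The article gives no dilution variance, and the 40% effect is also an assumption. This stands. A reader might infer that the change mostly reflects hydration, but the documents cannot show that: the share runs from minor to dominant over the ranges above. For a doubling, power stays high over much of the range.
- **No bias between groups.** Allocation is randomised and blinded, and nothing suggests that fluid intake differs by arm. This stands. A reader who infers a distorted treatment comparison goes too far; the harm is to precision and to within-group readings.
- **Correction does not restore full power.** This stands. Even perfect removal of dilution leaves 66% for a 40% rise at 19 v 19, and creatinine will not remove it perfectly.
- **Urine zinc may not be primary.** This stands in part. The Outcomes section and the Abstract point away from primary status, but the Primary objective section lists it and no section calls it secondary.
- **Absorption can be judged elsewhere.** A reader might infer that a null urine result could never be told from failure to absorb zinc. Serum zinc at both visits and pill counts partly answer that.
- **The article condenses a fuller protocol.** A correction could sit there. But specimen, occasions, assay and unit are all stated here, and together they define an uncorrected spot concentration.

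**Conclusion.** The point holds as an avoidable loss of precision in a listed outcome. As described, urine zinc is confounded with urine dilution, and the noise this adds is of unknown size. With o = 0.30 and d = 0.2 to 0.5 on the log scale, dilution accounts for about 31% to 74% of the variance of change. Power for a 40% rise in the pairwise comparison is then about 51% to 23%, against a ceiling of 66%.

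These figures rest on assumed SDs, an assumed effect and a log-scale analysis, which the article does not specify. They show what could be lost and do not estimate what will be. The stronger readings, that hydration dominates the change or that the group comparison is biased, are not supported. The sample size for FPG and the other outcomes are not affected.

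**What to change.** - Measure creatinine in the same urine specimen at both visits. Define the urine zinc outcome as the log of the zinc/creatinine ratio and analyse its change. Report the raw concentration descriptively only.
- Summarise the change as a ratio of geometric means, so that the noisy baseline does not inflate a mean percentage change.
- Reconcile the Abstract, the Primary objective section and the Outcomes section on whether urine zinc is a primary outcome.

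**Cost.** One routine assay on up to 84 × 2 = 168 specimens, with no added visit or sample. The ratio brings in creatinine assay error and differences in muscle mass; the latter should mostly cancel in change within a person.

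**Limit.** The Laboratory investigations section describes frozen storage for serum only and has urine zinc assayed straight after sampling. The Trial status section shows recruitment already under way. For participants whose earlier urine was not kept, correction at both visits may be impossible. The sponsor should check this first, and report the corrected outcome for those with both values, stating their number.

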### Dietary intake

Dietary intake will be recorded using 3-day food intake records (2 weekdays, 1 weekend day), which is a validated tool for diet analysis [51], at the baseline and at the end of the study by the participants (self-administered). The dietitian will train the participants to record the amount of food consumed with multiple homemade cutlery in order to enhance the accuracy of the portion size and review all entries in the food records. A blinded expert dietitian to the study allocation will review all forms of the completed 3-day food intake records. Dietary intake data will be analyzed using the Nutritionist IV software (version I) to estimate the energy and the number of macronutrients.

Also, they will be qualitatively recommended the dietary intake to improve dietary habits by messaging tools or telephone, weekly. The qualitative dietary recommendations will include (1) follow her/his diet, (2) avoid excessive intake of high-fat products (whole dairy products, poultry fat (the skin of chicken), red meat, butter, cream, ice cream, processed meats (sausages), coconut oil, and palm oil), and (3) avoid excessive sugar consumption (candy, soda, syrups, sugar-loaded desserts, caramels, and chocolate).

### Physical activity

The Short Form of International Physical Activity Questionnaire (IPAQ-SF), acceptable reliability and validity, will be used to assess total weekly PA [52] by a face-to-face interview. The IPAQ is suitable for adults between 15 and 69 years of age. IPAQ-SF includes four generic items (walking, moderate (such as leisure cycling), vigorous activities (such as aerobics), and sitting) and reported as minutes per week (min/week) within each activity category by a metabolic equivalent of task (MET) energy expenditure.

The following formula will be used to calculate the PA (MET min week^−1^):
$$ \mathrm{MET}\ \mathrm{level}\times \mathrm{duration}\times \mathrm{frequency}\ \mathrm{per}\ \mathrm{week}. $$

The results of PA will be categorized into 3 levels (vigorous-intensity activity, moderate-intensity activity, low-intensity activity) [53]. The participants will be interviewed by the blinded research staff to the study allocation to fill IPAQ-SF.

### Health-related quality of life

A validated and translated to Persian Short Form Health Survey (SF-36) questionnaire will be used to assess health-related quality of life (HRQOL) [54]. The assessment of HRQOL will show the patients’ overall health status, the impact of treatment, the formulation of health policy, and the decision on resource allocation [55]. Eight health-related dimensions will be measured by the SF-36 questionnaire that includes physical functioning (10 items), role limitations due to physical problems (4 items) and emotional problems (3 items), bodily pain (2 items), general health perceptions (5 items), vitality (4 items), social functioning (2 items), and perceived mental health (5 items). Also, there is a single item for health transition that provides an indication of perceived change in general health status over a 1-year period. The score of SF-36 will be obtained from the sum of the questions in eight domains. Scores range from 0 to 100. The participants with more or less disability will have lower or higher scores of SF-36, respectively [56].

### Participant adherence

At each follow-up visit, (1) participants will be briefed on the study guidelines (dietary and PA recommendation), adherence to the dosing schedule, dose timing, storage, and missed dose; (2) participants will be asked to return the unused supplementation and bottle; and (3) the importance of contacting the study assessor will also be noted in case of any problems (e.g., unusual symptoms). Adherence to the intake of the supplements will be assessed as good, moderate, or poor by pill counts (at 2nd, 3rd, and 4th visits). Participants will also be contacted daily with the methods mentioned earlier.

### Adverse events

Serious adverse events (SAE) with curcumin [19] or zinc supplementation [42] at the determined dosage have not been reported in the previous studies. However, all adverse events (AEs) including SAE and suspected unexpected serious adverse reaction (SUSAR) will be documented and reported to the Data Monitoring Committee (DMC) and the Ethics Committee of the Ahvaz Jundishapur University of Medical Sciences.

### Statistical analysis

Before statistical analysis, all data will be reviewed to check the accuracy and completeness. The primary analysis will be conducted on the intention-to-treat (ITT) population. Per-protocol (PP) and sensitivity analyses may be conducted as appropriate. The normality of data will be checked by the Kolmogorov-Smirnov test. The variables will be reported as mean ± SD or median (*Q*). The percentage changes for each variable will be separately reported and calculated by the following formula:
$$ \left[\left(E-B\right)/B\times 100\right], $$

where *E* and *B* are the end value and the baseline value of the variable, respectively.

According to the normality assumption, the significant changes between the groups will be assessed through a one-way analysis of variance (one-way ANOVA) with post hoc (LSD) analysis or Kruskal-Wallis. Changes from the baseline to post-intervention within the groups will be illustrated through a paired *t* test or Wilcoxon signed-rank test. The qualitative and quantitative variables in the two groups will be compared using the chi-square and *t* test, respectively. If necessary, the analysis of covariance (ANCOVA) will be used to control the potential confounding variables.

All analyses will be performed using a statistical software package (SPSS), version 22.0 (SPSS, Inc., Chicago, IL, USA), or NCSS2020. Statistical significance will be determined at *p* < 0.05.

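### Percentage change from baseline is prescribed for every variable, yet physical activity and SF-36 scores can be zero or very low at baseline, where the percentage is undefined or extreme (minor)

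*Protocol article*

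**What the plan says.** The Statistical analysis section of the protocol article sets one rule for all outcomes: "The percentage changes for each variable will be separately reported and calculated by the following formula". The formula is (E − B)/B × 100, where E and B "are the end value and the baseline value of the variable, respectively". It names no variable as an exception and does not say what happens when B is zero or close to it.

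The same section also summarises every variable by mean and SD or by median, so the percentage change is an additional figure. For inference it says that "the significant changes between the groups will be assessed through a one-way analysis of variance (one-way ANOVA) with post hoc (LSD) analysis or Kruskal-Wallis", without naming the scale of those changes. The Primary objective section reads: "The primary objective is to compare the mean changes in the serum levels of biochemical parameters". The Secondary objective section also speaks of mean changes.

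Two outcome sections define scales that include zero:

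- **Health-related quality of life:** for the SF-36, "Scores range from 0 to 100". Eight dimensions are listed, two of which (role limitations) have only 4 and 3 items.
- **Physical activity:** the IPAQ-SF items are "reported as minutes per week (min/week) within each activity category by a metabolic equivalent of task (MET) energy expenditure", and the score is the product of MET level, duration and weekly frequency.

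**The concern.** A percentage change makes sense for a quantity whose baseline is positive and well away from zero. FPG, HbA1c, lipids and weight qualify. A bounded questionnaire score and an activity total that may be nil do not.

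Three things can go wrong where the baseline is low:

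- At B = 0 the value does not exist, so the participant is absent from that summary. These are the people with the least activity or the worst domain score.
- Just above zero, a modest absolute change becomes hundreds of percent, and one person can set the group mean.
- Averaging E/B is asymmetric. A rise from a low baseline counts for far more than the equal fall back, so the mean percentage change can be clearly positive when nothing has changed on average.

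Low baselines followed by increases are plausible here. Participants have a BMI of 25 to 35 and are advised to reach 150 minutes of walking or cycling a week. At stake is whether the percentage figures for these outcomes can be read at face value.

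**Working it through.** The article prints no figure that depends on the percentage-change rule, so there is nothing of its own to reproduce. The sample size and alpha are not affected.

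**Inputs from the article.** The formula (E − B)/B × 100; SF-36 range 0 to 100; physical activity as a product of three terms, so 0 when no activity is reported; 21 participants per group (Sample size section).

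**Inputs that are assumed.** All individual baseline and end values, the SDs of the log ratio and the CVs below. The article gives no distributions for these outcomes.

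**1. Zero baseline.** SF-36 domain 0 → 25, or activity 0 → 600 MET-min/week: division by zero, so the value is undefined.

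**2. Low baseline.**
- SF-36 domain 25 → 100: 75/25 = +300%. Domain 75 → 100: 25/75 = +33%. The end score is the same, the absolute gains are 75 and 25 points, and the percentages differ ninefold.
- Activity 66 → 900: 834/66 = +1264%.
- For contrast, FPG 110 → 105: −5/110 = −4.5%, which is unremarkable.

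**3. One person in a group of 21.** With 20 participants unchanged and one going from 66 to 900, the mean is 1264/21 = +60% and the median is 0%.

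**4. No change on average.** Two participants swap 30 and 300 MET-min/week.
- Mean absolute change: (270 − 270)/2 = 0.
- Percentage changes: 270/30 = +900% and −270/300 = −90%. Mean: (900 − 90)/2 = +405%.

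**5. Skewed positive markers with no true change.** If ln(E/B) is normal with mean 0 and SD s, the expected percentage change is exp(s²/2) − 1.

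| s (assumed) | expected mean percentage change |
|---|---|
| 0.4 | +8.3% |
| 0.6 | +19.7% |
| 0.8 | +37.7% |

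A simulation (1,000,000 draws) with E and B independent and log-normal with the same CV gave:

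| CV (assumed) | mean percentage change | median |
|---|---|---|
| 0.08 | +0.7% | about 0% |
| 0.3 | +9% | about 0% |
| 0.6 | +36% | about 0% |
| 1.0 | about +100% | about 0% |

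The distortion is negligible for tightly distributed variables and grows with spread. The median removes it, but does not restore undefined values.

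**The case against.** The strongest reply is that percentage change is only a supplement. Every variable is also given as mean and SD or median, both objectives are framed as mean changes, and the tests are not said to use percentages. A participant with a zero baseline therefore stays in the main summaries and, on the natural reading, in the tests. Medians and Kruskal-Wallis are already allowed. With randomised arms sharing one baseline distribution, the upward shift under no effect is expected equally in all four groups and does not by itself bias the contrast between them. All of this stands, and it is why the point is minor.

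Two further replies stand in part.

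- **SF-36 scoring.** The article describes the score as a sum over the eight domains, which can be read as a total. A total of zero is implausible in adults aged 50 or less who were screened for major disease. The difficulty is therefore clearest for single domains and depends on their being scored separately. It does not affect the physical activity example.
- **A separate analysis plan.** Handling of zero denominators often sits there. But the article does more than stay silent: it fixes the percentage for each variable, and an analysis plan could cure that only by overriding the rule.

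A reader might also infer that IL-1B has zero baselines because values can fall below the assay limit. The Laboratory investigations section names the kit but gives no detection limit or expected level, so the documents do not support this.

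**Conclusion.** The rule is badly fixed for physical activity and for SF-36 scores. Applied as written, it gives undefined values at a zero baseline and unstable ones at a low baseline, and a mean percentage change can lie well above zero when nothing changes (+405% in the two-person swap; +60% from one participant in 21). These sizes are illustrations. How many participants will start at or near zero is unknown, and for skewed markers such as hs-CRP or insulin the size rests on assumed spreads. FPG, HbA1c, lipids and weight are little affected.

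The harm is confined to the reported within-group percentage figures unless the between-group tests are run on percentage change. The Statistical analysis section leaves that open, because percentage change is the only change it defines. The mean changes in the two objectives favour the absolute scale.

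Two stronger conclusions might be drawn, and neither is supported:

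- That the reported results will mislead. The absolute summaries stand beside the percentages, so the most one can say is that the percentage figures can mislead.
- That the intention-to-treat principle is breached. It is stated for the primary analysis, SF-36 and physical activity are secondary outcomes, and an undefined entry in an added descriptive summary removes nobody from a test.

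The severity is minor.

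**What to change.** Amend the Statistical analysis section as follows:

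- Limit percentage change to variables whose baseline is well away from zero, such as FPG, HbA1c, lipids and weight.
- Report absolute change for SF-36 scores and physical activity.
- Summarise skewed markers by the median or by the geometric mean ratio (end/baseline).
- State that the between-group tests use absolute change (or log-ratio change where a ratio is reported), and not percentage change.

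This costs a few sentences and needs no new data, and it leaves sample size, power and alpha as they are. The downside is that the measure of change then differs between rows of the results tables, so each row has to be labelled.
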